#### Who will take informed consent?

The informed consent process will be carried out either by the treating clinician or an appropriately trained member of the site research team. A treating clinician will provide eligible patients with the information and consent form for the trial. Patients will be given time to read the information and will be provided opportunities to clarify any concerns or ask questions prior to providing informed consent.

### Additional consent provisions for collection and use of participant data and biological specimens

Patients will be offered participation in two optional sub-studies. Patients will be asked to consent to participate in a sub-study which investigates the predictive power of a novel PET/CT scan using a novel CXCR4 tracer. Such a tracer has never been used in patients with cSCC in Australia. The result of this PET/CT scan will not impact on the treatment the patient receives, though the results obtained from this sub-study may be used to adjust treatment for future patients suffering from a similar condition. The CXCR4 PET/CT scans will be performed at baseline (prior to starting treatment) AND during week 3 of the treatment.

Patients will also be asked for a repeat core biopsy of the skin cancer or enlarged lymph node during the second week of treatment. Additional consent for this second biopsy will need to be obtained. The purpose is to identify any potential biomarkers in the biopsy specimen which may predict treatment response.

Participation in both sub-studies is optional. Patients who decline to participate in this sub-study will receive the same treatment as other study participants.

### Interventions

#### Explanation for the choice of comparators

Not applicable. This is a single arm study without a comparator.

#### Intervention description

Chemotherapy Platinum-based chemotherapy will commence on either day 1–3 of the radiation and preferably repeated on the same day of each week. A maximum of 7 weekly doses will be given. In cases where the chemotherapy is delayed or ceased, the radiotherapy will continue according to protocol. The primary chemotherapy regimen is cisplatin 40 mg/m^2^/week. Carboplatin may be used for patients with renal or cardiac or hearing impairment, at the discretion of the treating physician. Full blood counts, ELFT, magnesium, and renal function tests must be performed within 48 h prior to each weekly chemotherapy dose.

2.Immunotherapy Durvalumab will be supplied by AstraZeneca as a 500-mg vial solution for infusion after dilution. The solution contains 50 mg/mL durvalumab, 26 mM histidine/histidine hydrochloride, 275 mM trehalose dihydrate, and 0.02% weight/volume (w/v) polysorbate 80; it has a pH of 6.0. The nominal fill volume is 10.0 mL. Investigational product vials are stored at 2 to 8 °C (36 to 46°F) and must not be frozen. Drug products should be kept in secondary packaging until use to prevent excessive light exposure.Concurrent phase: administered every 4 weeks during chemoradiation (weeks 1 and 5).Adjuvant phase: same dose and frequency as concurrent phase in weeks 9,13 and 17. Up to 6 additional doses until the final disease status can be determined on PET/CT. Patients who achieve complete response or progressive disease will discontinue durvalumab immediately. Patients who undergo salvage surgery for residual disease will receive 6 more doses of durvalumab after surgery.Fixed dosing of 1500 mg every 4 weeks (approximate 20 mg/kg every 4 weeks)

3.Radiotherapy Intensity Modulated Radiotherapy (IMRT) should be utilised on all patients in the study cohort.

### Target volumes and doses

#### Locally advanced disease without nodal metastasis

Gross disease at the primary site: Gross Tumour Volume (GTV) should include all the imageable/palpable extent of the gross disease. In-transit dermal metastases, if evident, are to be included in the GTV. A recommended 5 mm margin is to be added to the GTV to form the Clinical Target Volume (CTV) to include any microscopic disease. CTV will then be expanded by 5 mm to form the Planning Target Volume (PTV), to account for any setup error and patient movement. Where possible, the PTV is to receive a total dose of 70 Gy in 35 fractions over 7 weeks as per ICRU 83 [34]. The dose variation across the PTV should not exceed + 7% and -5% of the prescription point (ICRU reference point dose). Where the location of the PTV precludes delivery of 70 Gy due to surrounding normal tissue constraint, a lower dose of 66 Gy in 33 fractions over 6.5 weeks is acceptable.

#### Prophylactic nodal irradiation

All attempts are to be made to include the first lymphatic draining echelon in the radiotherapy field (e.g. to include the parotid region when the primary disease is located at the temple). As these sites may harbour subclinical/microscopic disease, a total dose of 54 Gy in 35 fractions over 7 weeks, as per ICRU 83, is to be delivered. The dose variation across the PTV should not exceed + 7% and − 5% of the prescription point (ICRU reference point dose). The anatomical boundaries of cervical lymph node levels are to be defined as per Gregoire et al. [35].

#### Locally advanced disease or occult primary disease with nodal metastases

##### Gross disease at the primary site and macroscopically involved nodes

GTV should include all the imageable/palpable extent of the disease at the primary (skin) site and the macroscopically involved lymph nodes. In-transit dermal metastases, if evident, are to be included in the GTV. A recommended 5 mm margin is to be added to the GTV to form the CTV to include any microscopic disease. CTV will then be expanded by 5 mm to form the PTV, to account for any setup error and patient movement. Where possible, the PTV is to receive a total dose of 70 Gy in 35 fractions over 7 weeks as per ICRU 83. The dose variation across the PTV should not exceed + 7% and − 5% of the prescription point (ICRU reference point dose). Where the location of the PTV precludes delivery of 70 Gy due to surrounding normal tissue constraint, a lower dose of 66 Gy in 33 fractions over 6.5 weeks is acceptable.

##### Prophylactic nodal irradiation

The subsequent lymphatic draining echelons next to the involved nodal region should be included in the radiotherapy field (e.g. to include level II to III ipsilateral cervical lymph nodes when the parotid region is clinically involved). As these sites may harbour subclinical/microscopic disease, a total dose of 54 Gy in 35 fractions over 7 weeks, as per ICRU 83, is to be delivered. The level of cervical lymph nodes is to be defined as per Gregoire et al. [35].

##### Large nerve perineural spread (PNS)

The extent of PNS can be defined on 3 T Magnetic Resonance Imaging (MRI) and/or clinical examinations. The most commonly involved cranial nerves in the setting of head and neck cutaneous SCC are the fifth (Trigeminal) and the seventh (Facial) cranial nerves. PNS are to be encompassed in the CTV and a 5 mm margin should be added to form the PTV. However, a smaller margin of < 5 mm can be accepted if vital organs at risk are immediately adjacent to the PNS. Where possible, the involved nerve(s) should receive ≥ 66 Gy in 33 fractions. Where vital organs at risk (e.g. optic chiasm or brain stem) are immediately adjacent to the PNS, a lower dose between 54 Gy − 66 Gy in 2 Gy per fraction can be accepted.

The extent of elective nerve irradiation in continuity with the known PNS disease (Based on MRI and/or clinical examinations) is to be determined by the treating Radiation Oncologist. For example, a patient with evidence of right infraorbital nerve involvement may also receive elective radiotherapy to the proximal segment of V2 up to the trigeminal ganglion. The dose of elective nerve irradiation is generally between 50–60 Gy, respecting the surrounding vital organs at risk.

All radiotherapy target volumes will be peer reviewed and approved by another head and neck and skin Radiation Oncologist prior to planning.

### Criteria for discontinuing or modifying allocated interventions

Intervention safety monitoring and assessment Adverse events (AE), defined as any untoward medical occurrence(s) in a trial participant regardless of causality with trial interventions, will be systematically monitored and recorded. These will be classified and graded according to the National Cancer Institute Common Terminology Criteria for Adverse Events version 4.03 (NCI CTCAE v4.03).

Serious AEs (SAE) will be reported to the appropriate ethics committees and authorities as well as the study safety committee. A suspected unexpected serious adverse reaction (SUSAR), which is an unexpected SAE related to the intervention, will additionally be reported to the drug manufacturer. If the AE is deemed by the investigator to have been caused, or probably caused, by the investigational treatment (denosumab), this will be labelled a treatment-related adverse event (TRAE). Study participants will be reviewed clinically for the presence of AEs by the site investigator prior to each cycle of chemotherapy or immunotherapy. Blood tests, including complete blood count, liver and renal function tests, electrolytes, thyroid function tests and serum cortisol will be reviewed at these visits. Immune-related adverse events are managed following algorithms as compiled by expert groups or as available in the product information. Re-challenge after a suspected TRAE is permitted provided symptoms resolve to an appropriate level to meet criteria to resume treatment and do not meet any of the permanent discontinuation criteria (such as grade 4 and select grade 3 toxicities). Dose reductions and dose escalations are not permitted. An independent data safety monitoring committee will monitor the conduct and safety of the trial during recruitment.

#### Permanent discontinuation of study treatment

In the event of an infusion reaction of grade ≥ 3 severity during or directly following durvalumab infusion, dosing should be stopped and the patient must permanently discontinue durvalumab treatment.

Study treatment will be permanently stopped in the event of evidence of pregnancy.

In addition, study treatment for any patient may be discontinued for other safety reasons or compliance issues at the discretion of the investigator or sponsor. A patient may choose to discontinue study treatment or study participation at any time for any reason.

A patient who permanently discontinued durvalumab treatment should continue follow-up in the study without additional treatment until progression of disease, completion of all study assessments, or closure of the study.

#### Management of infusion/allergic/hypersensitivity reactions

Acute infusion reactions are defined as any AE that occurs during the infusion or within 2 h after the infusion is completed. Emergency equipment and medication for the treatment of these potential adverse effects (e.g. antihistamines, bronchodilators, intravenous saline, corticosteroids, paracetamol and/or adrenaline] must be available for immediate use. Infusion reactions must be reported as AEs and graded according to the NCI-CTCAE version 4.03 grading scale.

#### Termination of the infusion

The infusion should be terminated and NOT restarted if any of the following AEs occur: anaphylaxis, laryngeal/pharyngeal oedema, severe bronchospasm, chest pain, seizure, severe hypotension.

### Strategies to improve adherence to interventions

Regular review by the treating medical team (Medical and radiation oncology] and manage any toxicities early. Adjuvant phase of immunotherapy following completion of chemoradiation will require careful coordination and support to overcome logistical difficulties particularly for patients from out of town.

### Relevant concomitant care permitted or prohibited during the trial

Standard concomitant care to support patients through CRIO will be allowed such as standard anti-emetics for cisplatin and appropriate supportive care for patients undergoing chemoradiotherapy.

### Provisions for post-trial care

Patients will be followed up for a total of 5 years from the time of diagnosis (minimum 2 monthly in the first year, 3 monthly in the second year, and 6 monthly from years 3–5). Patients’ treating general practitioners and community will also be engaged in ongoing care particularly in the immediate four to six weeks after chemoradiation when ongoing skin dressings may still be required on a frequent basis.

### Outcomes

#### Primary outcome

To assess the safety of CRIO-incidence of treatment related toxicities
All treatment related toxicities will be recorded at each clinic visit for a total of two years in the Case Report Form using the CTCAE 4.03.To assess the rate of complete response

##### Patients with measurable disease

PET/CT scan +/− CT/MRI should be repeated at 19 (+/−2) weeks. Please refer to Fig. 1. Where results are equivocal, the clinician should either biopsy the suspected residual disease or repeat the imaging after an appropriate interval (week 27). The patient has achieved a CR if clinical and image findings are negative; if residual image findings are biopsy-negative; or if repeat imaging demonstrates resolution/stability of residual abnormalities.

**Fig. 1 Fig1:**
[figure not shown]
Consort diagram of CRIO trial

Patients who do not achieve a CR should be considered for salvage surgery. Patients who achieve CR after such surgery will be designated CR (Su) and will undergo follow up as above. Patients with residual disease which is unresectable will be recorded as having a treatment failure.

##### Patients with large nerve perineural spread

These patients are not eligible for assessment of complete response and will be assessed as progression-free or not based on symptoms and/or image findings. Clinical follow-up should occur as above. The first progress MRI should be performed at 3 months from completion of treatment and then 6 monthly thereafter.

Once a CR has been declared, patients should cease the Durvalumab and clinical follow-up at four weekly intervals for a total of 1 year from the start of treatment. The follow up schedule can be found in Table 1. Physical examination will include direct inspection and palpation of accessible sites. Imaging will be done if there is clinical suspicion of recurrence or progression. Biopsy or cytological confirmation of recurrent disease should be obtained whenever possible. The clinician will record disease status, sites and dates of any relapse and late effects of treatment.

**Table 1 Tab1:** Schedule of assessments

Investigation	Screening /Baseline	Wk 1	Wk2	Wk3	Wk4	Wk5	Wk6	Wk7	Wk9	Wk13	Wk17	Wk 19	Wk 21, 25, 29, 33, 37, 41	Wk 27	Months post treatment 2,4,6,8,10,12,15,18,21,24,30,36,42,48,54,60
Informed consent	x														
Histological confirmation of SCC	x														
Repeat biopsy (skin or lymph nodes]			× ^1^												
Medical history	x^6^														
Physical examination (ECOG, vital signs, toxicity]	x^6^	x	x	x	x	x	x	x	x	x	x		x		x
Concomitant meds	x														
Urine analysis	x														
Pregnancy test	x^6^														
FBC	x^6^	x	x	x	x	x	x	x	x	x	x		x		x^4^
U&E, LFT’s	x^6^	x	x	x	x	x	x	x	x	x	x		x		x^4^
Coagulation profile, TSH, hep, HIV															
x															
FDG PET	x^7^											x		x^2^	
CXCR4 PET /CT	x^3^			x											
Contrast CT / MRI	x^7^											x^4^			
Disease status		x	x	x	x	x	x	x	x	x	x		x		x
Blood	x			x						x			x^5^		

^1^Not mandatory

^2^If week 19 FDG PET is equivocal

^3^Pretreatment

^4^If clinically indicated

^5^Weeks 21 and 37 only

^6^Due within 14 days of trial registration

^7^Due within 28 days of trial registration

Patients who are considered treatment failures will be followed at the above time points for survival only. This may be done at clinic visits when seen for ongoing treatment or by telephone call

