#### Eligibility criteria

Inclusion criteria were as follows: adult patients presenting with pathologically confirmed unresectable* cSCC with locally-advanced disease at the primary site with or without metastases to the nodal regions, or advanced regional lymph node metastases of presumed skin origin, or unresectable perineural disease (stage III-IVa); Eastern Cooperative Oncology Group performance status 0–2; and assessable disease. Patients with bulky disease are assessed using RECIST criteria. Patients with perineural disease must have disease visible on imaging or biopsy-proven disease.

Exclusion Criteria include: Immunosuppression secondary to haematological malignancy or the use of immunosuppressant following solid organ transplantation; active infection requiring therapy with HIV, Hepatitis B or C virus; active uncontrolled bleeding; previous chemotherapy and/or radiotherapy to the head and neck region which would preclude re-treatment; contra-indication for radiotherapy or chemotherapy; claustrophobia; previous treatment with a PD1 or PD-L1 inhibitor; receipt of anticancer therapy 60 days prior to the first dose of study drug; use of immunosuppressive medication within 14 days before the first dose of Durvalumab (MEDI4736); any unresolved toxicity NCI CTCAE v 4.03 Grade ≥ 2 from previous anticancer therapy; history of allogenic organ transplantation; active or prior documented autoimmune or inflammatory disorders and receipt of recent live attenuated vaccine.

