#### Sample size

A two-stage minimax design will be applied, which requires an initial sample of 15 patients, with possibly an additional 13 patients required (total 28) subject to feasibility. The hypothesis that the proportion responding is 70% or more compared to the alternative hypothesis that 50% or fewer respond will be tested using a two sided binomial test with a target significance level of 0.10 and power of 0.80. Fifteen patients would be recruited in the first stage and if 7 or fewer patients respond the trial will be terminated and we will conclude that the treatment is not more effective than standard treatment. If 8 or more patients respond, the trial may go to the second stage, recruiting a further 13 patients. Of the total of 28 patients, 18 or more must respond to the treatment to be considered better than current treatment. Sample size was calculated using the PASS 13 Power Analysis and Sample Size Software (NCSS, 2014).

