#### Methods in analysis to handle protocol non-adherence and any statistical methods to handle missing data

The primary analysis will be intention-to treat, with all patients included, regardless of adherence to the protocol. A per protocol analysis will be conducted as a sensitivity analysis for the proportion of patients showing CR.

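### The complete-response denominator is contradictory: patients with large nerve perineural spread are enrolled and kept in the all-patient primary analysis, but cannot be assessed for complete response

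*Protocol article*

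**What the plan says.** All references are to the protocol article.

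- **Eligibility criteria.** One inclusion route is "or unresectable perineural disease (stage III-IVa"). The same section adds: "Patients with perineural disease must have disease visible on imaging or biopsy-proven disease". The definition of unresectable disease uses big nerve perineural spread as an example, and the radiotherapy section gives large nerve spread its own target-volume rules. The group is expected, not incidental.
- **Outcomes, large nerve perineural spread.** "These patients are not eligible for assessment of complete response and will be assessed as progression-free or not". The CR criteria themselves stand under a separate heading for measurable disease.
- **Sample size.** The two-stage rule is written on patients recruited: "Fifteen patients would be recruited in the first stage and if 7 or fewer patients respond the trial will be terminated". With 8 or more responses a further 13 may be recruited, and 18 of the total of 28 must respond.
- **Handling of non-adherence and missing data.** "The primary analysis will be intention-to treat, with all patients included, regardless of adherence to the protocol".
- **Statistical methods.** The CR proportion is compared with 0.5 by an exact binomial test.

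The article does not take these patients out of the CR denominator, replace them, cap their number, count progression-free status as a response, or allow for them in the sample size.

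**The concern.** CR is a co-primary endpoint and the only one with a numerical stop/go rule and success rule. Both rules are counts, so they have meaning only against a known denominator. Here one part of the article defines the endpoint for a subset of enrolled patients, while another analyses everyone and sets the boundaries on everyone.

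Two things are at stake. Case mix could stop the trial at stage 1, or fail it at the end, although the regimen performs as hoped in patients who can be assessed. And in a non-blinded single-centre trial, an open denominator leaves room to settle it after responses are known.

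**Working it through.** **Inputs from the article.** Null rate 0.50 and target rate 0.70; stage 1 of 15 patients, stop at 7 or fewer; total 28, success at 18 or more; significance level 0.10; power 0.80.

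**Inputs not in the article, so assumed.** (a) The 70% and 50% rates apply to assessable patients. (b) The number or share of patients with large nerve spread; a range is shown.

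**Step 1: reproduce the plan's design.** With m1 and m2 patients able to respond in stages 1 and 2,

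P(success) = sum over x from 8 to m1 of P[Bin(m1, p) = x] × P[Bin(m2, p) ≥ 18 − x].

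With m1 = 15 and m2 = 13, p = 0.50 gives 0.090 and p = 0.70 gives 0.801. The chance of stopping at stage 1 when p = 0.70 is P[Bin(15, 0.70) ≤ 7] = 0.050. An exact minimax search at one-sided 0.10 returns this same design. The stated power is therefore reproduced when every recruited patient responds with probability 0.70.

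**Step 2: perineural patients in the denominator, none able to respond, fixed counts.** The boundaries stay at 8 and 18; only m1 and m2 shrink.

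| Perineural patients (stage 1 + stage 2) | m1, m2 | Power at 0.70 | Type I error at 0.50 |
|---|---|---|---|
| 0 + 0 | 15, 13 | 0.801 | 0.090 |
| 1 + 0 | 14, 13 | 0.714 | 0.058 |
| 1 + 1 | 14, 12 | 0.622 | 0.037 |

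**Step 3: the same, by expected share f.** Each recruited patient responds with probability 0.70 × (1 − f), or 0.50 × (1 − f) under the null.

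| f | 0.70 × (1 − f) | Power | Stop at stage 1 | Type I error |
|---|---|---|---|---|
| 0% | 0.700 | 0.801 | 5% | 0.090 |
| 5% | 0.665 | 0.670 | 9% | 0.054 |
| 10% | 0.630 | 0.520 | 15% | 0.031 |
| 20% | 0.560 | 0.240 | 32% | 0.008 |

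**Step 4: the other reading, patients dropped and not replaced.** With 1 + 1 dropped, 14 and then 26 patients are assessed. If 8 and 18 still apply, the required counts are those of step 2 and power is again 0.622. If they do not apply, the article gives no others.

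**Step 5: boundaries refitted to 14 and 26 assessable.** Stop at 6 or fewer of 14, succeed at 17 or more of 26. The same formula gives type I error 0.084 and power 0.768.

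**The case against.** The strongest reply is that the article never says these patients count as non-responders. The all-patients sentence sits under a heading on non-adherence and missing data, and the CR criteria sit under measurable disease, so a CR proportion among assessable patients is a plausible intention. That stands: non-response is inferred from two passages together. But the intention is not written down, and it contradicts both the all-patients sentence and boundaries set on recruited patients.

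A reader might also infer that power of 0.80 holds only if no such patient is enrolled. The documents do not support that. The sample size section applies 70% and 50% to the proportion responding, without restricting it to measurable disease. The 50% comes from the institution's earlier chemoradiation study, which the Discussion describes as a similar cohort; the article does not say how that study handled perineural disease. If both rates are already all-comer rates, power remains 0.80. The implied rate among assessable patients would then be 0.70/0.90 = 78% at a 10% share and 0.70/0.80 = 88% at 20%.

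Third, the share is unknown. The bar covers large nerve spread, whereas eligibility speaks of perineural disease more broadly, and a patient with both nerve spread and bulky disease may be assessable. The 20% row has no anchor in the article and is illustrative only. These points limit the size, not the existence, of the contradiction. The co-primary safety endpoint is unaffected.

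**Conclusion.** The contradiction is in the text and needs correcting. Neither counting these patients as non-responders nor dropping them matches the stated boundaries to the number of patients who can be assessed.

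The power loss is conditional on assumptions (a) and (b). Under them a single perineural patient in stage 1 costs about 9 percentage points of power (0.80 to 0.71), and a 10% share costs about 28 (0.80 to 0.52). Type I error falls as well, so the risk is of wrongly stopping or rejecting an effective regimen, not of a false claim of benefit. The article does not establish that power is in fact below 0.80, because neither the share nor the benchmark's denominator is given.

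**What to change.** Before further response data are reviewed, amend the wording to:

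1. Define the primary CR set as all enrolled patients with CR-assessable disease, regardless of adherence.
2. State how patients with both measurable and perineural disease are classed.
3. Confirm that the 50% benchmark was computed on the same denominator; if it was not, restate the null and target rates for the chosen set.
4. Keep total enrolment as planned, prespecify boundaries for each attainable assessable number, and restate power. For 14 and 26 assessable, for example: stop at 6 or fewer, succeed at 17 or more, type I error 0.084, power 0.77.
5. Report patients with large nerve spread separately (progression-free proportion and safety), and give the all-patient CR proportion as a sensitivity analysis.

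**Cost.** Protocol wording and a slightly lower stated power. Since accrual began in May 2019, the amendment should be dated and should record which response data had been seen.

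Filling all 28 places with assessable patients would keep power at 0.80 but is optional, because accrual is slow. At the planned 15 patients in 24 months (0.625 per month), a 10% share needs 28/0.90 − 28 = 3.1 more patients, about 5 months; a 20% share needs 28/0.80 − 28 = 7 more, about 11 months.

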### Definition of treatment failure

The patient will be considered as having treatment failure if:Progressive disease at any time;Residual disease at 12 weeks and not amenable to salvage surgery;Recurrent disease within the irradiated field during follow up that is biopsy-proven or increases over serial imaging/clinical examination;Metastatic disease

Secondary Outcomes include overall Survival, progression free survival, and locoregional control will be assessed.

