### Data collection and management

#### Plans for assessment and collection of outcomes

As per schedule of assessments (Table 1). All treatment related toxicities will be recorded at each clinic visit for a total of two years in the Case Report Form using the CTCAE 4.03. (https://evs.nci.nih.gov/ftp1/CTCAE/CTCAE_4.03_2010-06-14_QuickReference_8.5x11.pdf).

Disease status of patients will be recorded at each visit during and after completion of treatment.

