### Statistical methods

#### Statistical methods for primary and secondary outcomes

For the first stage, the analysis will focus on descriptive statistics. Categorical variables will be summarised using frequencies and percentages and continuous variables will be summarised using means with standard deviations or as medians with interquartile ranges. Median survival time (with 95% CI) will be described and survival time will be presented using a Kaplan–Meier curve. Safety/toxicity data will be presented according to the frequency of occurrence. The proportion of patients experiencing the primary outcome (complete response) will be presented with 95% confidence intervals and compared to the hypothesized null effect of 0.5 using an exact binomial test.

Secondary outcomes including overall survival, disease free survival, time to progression and loco-regional control will be presented using a Kaplan–Meier curve.

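### Survival-only follow-up after treatment failure leaves the date of later progression uncollected for patients with unresectable, non-progressed residual disease, although PFS and time to progression are secondary outcomes

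*Protocol article*

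**What the plan says.** Under Patients with measurable disease, in the text below Fig. 1, the article states: "Patients with residual disease which is unresectable will be recorded as having a treatment failure". The section Definition of treatment failure gives four routes to failure. One is "Progressive disease at any time". A separate one is "Residual disease at 12 weeks and not amenable to salvage surgery". The other two are recurrence within the irradiated field and metastatic disease.

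The text below Table 1 sets the follow-up after failure: "Patients who are considered treatment failures will be followed at the above time points for survival only". It adds: "This may be done at clinic visits when seen for ongoing treatment or by telephone call".

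Two other places describe disease follow-up differently.
- Plans for assessment and collection of outcomes: "Disease status of patients will be recorded at each visit during and after completion of treatment".
- Permanent discontinuation of study treatment: patients who permanently stop durvalumab stay in follow-up until progression, completion of the assessments or study closure.

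Table 1 carries a disease-status row through weeks 21 to 41 and the post-treatment visits to month 60.

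On the endpoints, Definition of treatment failure ends: "Secondary Outcomes include overall Survival, progression free survival, and locoregional control will be assessed". Statistical methods for primary and secondary outcomes says that "overall survival, disease free survival, time to progression and loco-regional control will be presented using a" Kaplan–Meier curve.

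**The concern.** Three of the four failure routes (progression, in-field recurrence, metastasis) are already disease events, so survival-only follow-up after them costs PFS nothing. The fourth is different. A patient whose unresectable residual disease is stable or shrinking has failed treatment without progressing. From then on the follow-up rule asks only whether the patient is alive, so the date of a later progression need not be recorded.

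This is a stated data-collection rule. An analysis plan can define events and censoring, but it cannot recover progression dates that the site was told not to collect. The patients affected are plausibly more likely to progress than complete responders. If they are censored at failure, the censoring is informative. If only their deaths count, their PFS becomes overall survival. Either way the PFS curve is too high. For time to progression, where death is not usually an event, they would contribute only censored time.

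**Working it through.** **Reading the passages together**

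| Failure route | Already a PFS event? | Lost under survival-only follow-up |
|---|---|---|
| Progressive disease | Yes | Nothing needed for PFS |
| In-field recurrence | Yes | Nothing needed for PFS |
| Metastatic disease | Yes | Nothing needed for PFS |
| Unresectable residual disease, not progressed | Not stated | Date of later progression |

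The survival-only sentence is specific to failures. Neither the general statement on recording disease status nor the rule for patients who stop durvalumab clearly overrides it, so two defensible readings would collect different data.

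**How many patients are exposed**

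The plan states no PFS figure. Its Sample size section gives a 50% null and a 70% target complete response (CR) rate, 15 patients in stage one and 28 in total. That design reproduces: a minimax search returns 15/28, stopping at 7 or fewer and succeeding at 18 or more, with a one-sided level of 0.0900 and power of 0.8009. It does not involve PFS.

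An upper bound on the exposed group is all patients without CR:
- 28 × (1 − 0.70) = 8.4 and 28 × (1 − 0.50) = 14.
- If the trial stops at 15: 15 × 0.30 = 4.5 and 15 × 0.50 = 7.5.

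This takes every patient as assessed for CR. Patients with large nerve perineural spread are not, so the bound is approximate.

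**Illustration of the effect on 24-month PFS**

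Assumptions, none from the documents: 80% of complete responders are progression-free at 24 months; 10% of residual-disease patients are progression-free and 40% are alive; all other non-CR patients have an event by the response assessment. Let c be the CR rate and s the share of non-CR patients with unresectable, non-progressed residual disease. Write r = (1 − c)s and e = (1 − c)(1 − s).

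- Failure counted as the event: 0.8c
- Full disease follow-up: 0.8c + 0.1r
- Only deaths counted: 0.8c + 0.4r
- Censored at failure: 0.8(1 − e)

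| c | s | Failure as event | Full follow-up | Deaths only | Censored |
|---|---|---|---|---|---|
| 0.50 | 0.25 | 0.400 | 0.413 | 0.450 | 0.500 |
| 0.50 | 0.50 | 0.400 | 0.425 | 0.500 | 0.600 |
| 0.70 | 0.25 | 0.560 | 0.567 | 0.590 | 0.620 |
| 0.70 | 0.50 | 0.560 | 0.575 | 0.620 | 0.680 |

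Example for c = s = 0.50: r = e = 0.25. Full follow-up gives 0.40 + 0.025 = 0.425, deaths only 0.40 + 0.10 = 0.50, and censoring 0.8 × 0.75 = 0.60.

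Against full follow-up at s = 0.50, censoring adds 17.5 points (c = 0.50) or 10.5 points (c = 0.70), and counting only deaths adds 7.5 or 4.5 points. At s = 0 every difference is zero. For scale, the binomial standard error with 28 patients at 0.425 or 0.575 is √(0.425 × 0.575 / 28) = 0.093.

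**The case against.** The strongest reply is that treatment failure is itself the disease event. The failure definition stands directly above the sentence naming PFS and locoregional control, and survival-only follow-up would then be coherent because only death remains to be collected. Event and censoring rules may also sit in an analysis plan or full protocol that is not shown. This stands in part: the article does not prescribe censoring at the week 19 scan or anywhere else, and if failure is the event, PFS can be scored in full. The reply does not remove the conflict over what is recorded after failure. Nor does it help if the unseen plan requires a progression date.

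A reader might infer that PFS cannot be scored at all for these patients. The text does not support that: deaths are captured, and some disease information may still be noted at clinic visits.

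A reader might also infer that every such patient leaves disease assessment at about week 19. That is not established. Equivocal scans may be settled at week 27, the intervention text allows further durvalumab doses until final disease status is determined, and Table 1 schedules disease status through week 41.

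Locoregional control might be thought equally biased. It is little affected here, because persistent local disease can naturally be counted as not controlled. Whether to record local status after a first distant failure is a choice of analysis, not an error.

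Finally, these are secondary endpoints shown descriptively in 15 to 28 patients without a comparator. That is correct and limits the weight of the point.

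**Conclusion.** The point holds in a limited form. For failures with non-progressed, unresectable residual disease, the follow-up rule does not collect the date of later progression, although PFS and time to progression are secondary outcomes. It contradicts the statement that disease status is recorded at each visit, and it is not reconciled with follow-up until progression after durvalumab is permanently stopped.

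If residual-disease failure is not a PFS event, the direction of bias is upward, provided these patients progress sooner than complete responders. The amount cannot be derived from the documents. The illustration runs from near zero to more than 10 points and depends wholly on assumed rates, so no single figure should be presented as an estimate. If failure is the event, the PFS bias disappears and only the conflict in the text remains.

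The CR rate, the safety endpoint and the rule of 18 or more of 28 are unaffected. This should be corrected, but it does not threaten the trial's main conclusion.

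**What to change.** One of two changes is enough.

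1. Amend the survival-only sentence below Table 1 so that treatment failures without documented progression keep the Table 1 disease-status recording until progression or death. Reconcile it with Permanent discontinuation of study treatment and with Plans for assessment and collection of outcomes.
2. If disease follow-up is meant to stop at failure, state in Definition of treatment failure and in Statistical methods for primary and secondary outcomes that unresectable residual disease is an event for PFS and locoregional control, dated at the assessment that established it, and not a censoring. Reword the each-visit statement on disease status to match.

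The first costs a few clinic assessments in place of telephone calls; the visits and the disease-status row already exist. Table 1 has no routine imaging after weeks 19 and 27 for measurable disease, so later progression would be found mainly on clinical grounds. The second needs no extra data but gives a less favourable PFS curve (0.400 against 0.425 in the illustration with c = s = 0.50).
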